# Chlorhexidine vaginal preparation versus standard treatment at caesarean section to reduce endometritis and prevent sepsis—a feasibility study protocol (the PREPS trial)

**DOI:** 10.1186/s40814-018-0273-9

**Published:** 2018-06-04

**Keywords:** Caesarean section, Chlorhexidine, Endometritis, Sepsis, Post-natal infection, Vaginal cleansing, Feasibility

## Abstract

**Background:**

Worldwide caesarean section (CS) delivery is the most common major operation. Approximately 25% of pregnant women undergo a CS in the UK for delivery of their babies. Sepsis and post-natal infection constitute significant maternal mortality and morbidity. Infection following a CS has a number of primary sources including endometritis occurring in 7–17% of women. Sepsis reduction and reduction in antibiotic use have been identified as a national and international priority. The overarching aim of this research is to reduce infectious morbidity from caesarean sections.

**Methods:**

This is a parallel group feasibility randomised controlled trial comparing vaginal cleansing using chlorhexidine gluconate versus no cleansing (standard practice) at CS to reduce infection. Women will be recruited from four National Health Service maternity units. Two hundred fifty women (125 in each arm) undergoing elective or emergency CS, who are aged 16 years and above, and at least 34 weeks pregnant will be randomised. Allocation to treatment will be on a 1:1 ratio. The study includes a qualitative aspect to develop women centred outcomes of wellbeing after delivery.

**Discussion:**

The success of the feasibility study will be assessed by criteria related to the feasibility measurements to ascertain if a larger study is feasible in its current format, needs modification or is unfeasible, and includes recruitment, adherence, follow-up and withdrawal measures.

**Trial registration:**

The PREPS trial has been registered with ISRCTN (ISRCTN 33435996).

## Background

### Justification for participant population

Worldwide caesarean section (CS) delivery is the most common major operation. Approximately 25% of pregnant women undergo a CS in the UK for delivery of their babies. This equates to approximately 171,000 caesarean sections per year in England alone.

Sepsis and post-natal infection constitute significant maternal mortality and morbidity, as well as having significant impact on post-natal recovery and maternal wellbeing. Infection following a CS has numerous primary sources including endometritis, occurring in 7–17% of women; this equates to approximately 27,000 cases of infection per year in England only. Risk factors for endometritis following CS include in labour caesarean section and ruptured membranes with or without vaginal colonisation with group B streptococcus. Sepsis reduction and reduction in antibiotic use have been identified as national and international priorities, improving maternal health and neonatal wellbeing through the facilitation of ongoing breast feeding.

### Justification for intervention

Prophylactic antibiotics at the time of surgery have been demonstrated to be beneficial in a number of large randomised controlled trials (RCT) and continue to reduce infection rates [1]. Current practice of skin preparation [2] is guided by a recent RCT demonstrating the superiority of a chlorhexidine over an iodine-based solution [3]. In addition to skin preparation with an antiseptic solution, cleansing inside the vagina with povidone iodine has been evaluated [4]. A Cochrane review of seven trials randomising 2816 women (2635 analysed) estimated the effects of vaginal cleansing (all with povidone-iodine) on post-caesarean infectious morbidity [4]. Vaginal preparation immediately before caesarean delivery significantly reduced the incidence of post-caesarean endometritis from 8.3% in control groups to 4.3% in vaginal cleansing groups (average risk ratio (RR) 0.45, 95% confidence interval (CI) 0.25 to 0.81, seven trials, 2635 women). The risk reduction was particularly strong for women who were already in labour at the time of the caesarean delivery (7.4% in the vaginal cleansing group versus 13.0% in the control group; RR 0.56, 95% CI 0.34 to 0.95, three trials, 523 women) and for women with ruptured membranes (4.3% in the vaginal cleansing group versus 17.9% in the control group; RR 0.24, 95% CI 0.10 to 0.55, three trials, 272 women [4]). The above would appear an effective and important strategy to reduce morbidity at CS, yet this has not been adopted within obstetric practice internationally and does not feature within the NICE Intrapartum guideline [5]. This is due to concerns with exposure of the fetus to iodine-based substances, concerns with vaginal staining and allergy to iodine. Iodine is a recognised antibacterial agent, but inactivity by the presence of blood [6] limits its use. Thus, there are a number of reasons to believe that vaginal cleansing with chlorhexidine would be an appropriate alternative to povidone iodine. Some studies show greater reduction in skin flora after application of chlorhexidine (0.5 and 4%) [6] compared with povidone-iodine agents. Also, chlorhexidine may have a greater residual activity after application than other preparations and, unlike povidone iodine, it is not inactivated by the presence of blood. Solutions that contain lower concentrations, such as the commonly used chlorhexidine gluconate and acetate (0.05%), are usually well tolerated and may be used for vaginal preparation [6]. With this preparation, there are no reported cases of allergy. There is one small randomised controlled trial comparing povidone iodine with chlorohexidine gluconate for vaginal cleansing at CS. This suggested that chlorohexidine may be superior, and further research was needed [7].

A Cochrane review of cleansing the vagina in normal vaginal delivery with chlorhexidine showed no evidence of an effect on maternal or neonatal infections with low to moderate confidence, although further large scale trials to detect small but clinically important differences were needed. Importantly, no safety concerns for the mother or baby have been identified within these studies [8].

## Methods

### Aims

The overarching aim of this research is to reduce infectious morbidity from caesarean sections. Specific objectives for this feasibility study include:To determine appropriate recruitment and randomisation processesTo assess if women can remain blinded to the trial interventionTo determine the sample size required for a definitive trialTo inform if the intervention can be conducted in a multi-centre RCTTo develop women focused outcome measures and method of data collectionTo assess data collection of clinical outcomes up to 6 weeksTo assess withdrawals

### Qualitative study design

A qualitative study will inform the outcomes that will be collected on women in the feasibility RCT. Two focus groups will be performed at the lead site (Birmingham Women’s and Children’s Hospital BWCH) of approximately 7 to 10 women in each group who have undergone a CS and would like to contribute to the development of women-centred outcomes.

Women will be recruited via adverts placed on BWCH notice boards and on the post-natal wards, through social media platforms; community midwives will be asked to identify women, as well as hospital midwives if women re-attend and through patient engagement services at BWCH. We will ask women who have had a CS within the previous 6 months to contribute to focus groups on important women-centred outcomes for research into infection and complications following a CS.

The focus groups will be performed prior to commencement of recruitment to the feasibility RCT and thus used to decide on outcomes for inclusion in the feasibility trial that the women feel are important for post-natal quality of life and recovery. All women will have demographic data collected. The focus groups will be recorded and transcribed anonymously. The data will be analysed thematically and managed using the Framework Method [9]. An experienced qualitative researcher will run the focus groups, with the support of a research associate and the clinical research fellow.

From informal discussions with women who have undergone CS, the outcomes are likely to be composed of the following themes:Length of midwife follow-upProlonged use of analgesicsAbility to care for selfTime to leaving house with family/independentlyAbility to care for a baby

### Feasibility study design

Blinded to women and personnel performing outcome collection, parallel group, feasibility RCT compared vaginal cleansing using chlorhexidine gluconate or acetate versus no cleansing (standard practice) at CS to reduce infection. Allocation to treatment will be on a 1:1 ratio. A feasibility randomised controlled trial design is being undertaken to test the consent and randomisation processes for women requiring a CS, and the follow-up processes up until the immediate post-natal period, to ensure we can overcome the challenges this poses.

### Trial setting

The trial will be undertaken in maternity hospitals: Birmingham Women’s and Children’s Hospital, Birmingham Heartlands Hospital, Shrewsbury and Telford Hospital (West Midlands) and Sunderland Royal Hospital, to ensure the trial can be extrapolated to a larger multi-centre trial.

### Identification of participants

Given recruitment, consent and randomisation processes will differ for emergency and elective CS due to differences in planning for surgery; the processes for each type of surgery will be detailed separately. All women booking at any of the hospitals over the study period and who are greater than 34 weeks pregnant while recruitment is running will be posted a patient information leaflet. This is to ensure that all women are aware of the study before delivery of their baby/babies. This will be accompanied with patient information leaflets and study information being available in antenatal clinics and triage waiting rooms. Study posters will also be displayed in prominent positions through the hospitals.

### Eligibility criteria and co-enrolment

Women will be included in the trial if they are as follows:Greater than or equal to 34 weeks pregnantHaving a CSAble to give informed written consentAble to receive a telephone interview at 14 and 30 days post-natalAged 16 years or over

Women will be excluded from the trial if they:Have a known allergy to chlorhexidine gluconate or any of its ingredientsAre receiving prophylactic intravenous antibiotics for group B streptococcus (GBS) colonisationAre receiving intravenous antibiotics for suspected infection (standard CS intravenous prophylaxis is not an exclusion criteria)Are currently enrolled in an RCT for an intervention intended to reduce post-operative surgical site infection

All women already enrolled in an interventional study are permitted to be co-enrolled into PREPS, as long as the intervention is not intended to reduce infection. After consent and randomisation to PREPS, women will not be permitted to enter a further interventional study if the study is evaluating the prevention of infection. Co-enrolment in all observational studies is permitted.

### Randomisation

After the woman’s eligibility has been confirmed and informed consent has been received, the woman can be randomised into the trial (Fig. 1). Randomisation can be performed by all members of the research team and clinical team and is most likely to be performed by dedicated research midwives.

**Fig. 1 Fig1:**
[figure not shown]
Trial participant flow

Randomisation will be provided by a secure automated telephone randomisation system available 24 h a day/7 days a week provided by the University of Aberdeen. The telephone randomisation service will comply with research and governance standards.

The randomised allocation will be documented in the main hospital records on the anaesthetic chart, on a dedicated sticker within the patient notes and on the relevant case report forms. The allocation will not be disclosed to the woman or recorded in the post-natal hand-held notes.

Women will be randomised at the level of the individual in a 1:1 ratio to either chlorohexidine gluconate or acetate 0.05% vaginal cleansing or standard treatment of no vaginal cleansing. A minimisation algorithm will be used to ensure balance in the treatment allocation over the following variables:Randomising centreIn labour and not in labour CS

A ‘random element’ will be included in the minimisation algorithm so that each patient has a probability (unspecified here) of being randomised to the opposite treatment that they would have otherwise received.

### Blinding

The trial cannot be blinded to the operator or the clinical care team in theatre providing care to the women due to the nature of the intervention. Randomisation will be performed by a wide range of staff from theatre runners to consultants. Randomisation may be performed by dedicated research midwives who will also collect outcome data from the notes, but there will be no recording of the allocation in the post-natal notes.

Attempts will be made to blind the women as the intervention will be applied at the time of the catheter insertion, and the woman should not be aware of the application due to anaesthesia.

All data collection from the maternal notes will be blinded since there will only be recording of whether the intervention was applied on the theatre operation note and anaesthetic/operation chart, which are not held in the maternal post-natal notes. As a part of the monitoring process, 10% of medical records will be independently monitored and data collection will be verified by the trial sponsor on-site.

The research midwife conducting the telephone follow-up interviews will be blinded to the treatment group so that there will be no bias in the collection of outcomes. The research midwife will not have an access to the medical records or any data collection forms at the time of telephone interviews.

At the end of the 14-day interview, the midwife will ask the woman whether she feels she received the intervention or not to assess whether blinding of the woman is an achievable aim.

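### Outcome collection from the notes is declared blinded, but the plan lets the midwife who randomised a woman also abstract her outcomes

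*Protocol article*

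**What the plan says.** The Feasibility study design section opens with the label "Blinded to women and personnel performing outcome collection, parallel group, feasibility RCT". The Blinding section supports it for notes abstraction: "All data collection from the maternal notes will be blinded since there will only be recording of whether the intervention was applied", with the theatre operation note and anaesthetic/operation chart given as the only places of record, and with the remark that these are kept apart from the post-natal notes.

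On who does the work, the Randomisation section says that randomisation "is most likely to be performed by dedicated research midwives". The Blinding section adds "Randomisation may be performed by dedicated research midwives who will also collect outcome data from the notes" and follows this with the assurance that the post-natal notes will not show the allocation. It also says that randomising staff will range from theatre runners to consultants.

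On where the allocation is written, the Randomisation section lists the anaesthetic chart in the main hospital records and then "on a dedicated sticker within the patient notes and on the relevant case report forms". It adds: "The allocation will not be disclosed to the woman or recorded in the post-natal hand-held notes".

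Telephone interviews are treated separately. The Blinding section requires the interviewing midwife to be blinded and denies her access to records and data collection forms at the time of the interview.

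**The concern.** Blinding of an outcome collector depends on what that person knows, and the set of notes in front of her is only one source of that knowledge. The Blinding section recognises that a midwife may randomise and later abstract, but it answers with a rule about what the post-natal notes contain. That protects an abstractor who never learned the arm. It does nothing for one who was given it.

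The clinical outcome most exposed is the proposed primary outcome of the full trial. The Clinical outcomes section separates endometritis that meets the CDC definition from endometritis diagnosed by a clinician that does not meet it or cannot be verified to meet it. If that sorting is done from the notes, it involves judgement, and knowledge of the arm could tilt it.

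The process could also pass unexamined into the main trial. The Aims and Other feasibility outcomes sections test blinding in the women only; neither lists a check on the people collecting outcomes. Under the Traffic light system, a green light means going ahead with the protocol unchanged, apart from a clear message from the focus groups.

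**Working it through.** No sample size, error rate or power figure is involved, so the check is a comparison of the article's statements.

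**1. What is claimed.** Feasibility study design: outcome collectors are blinded. Blinding: all collection from the maternal notes is blinded. Neither statement carries an exception.

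**2. Who learns the allocation.** Randomisation: "Randomisation will be provided by a secure automated telephone randomisation system". I assume that the person who randomises is told the result, since it must then be written on the chart and acted on. The Blinding section adds that the operator and the theatre care team cannot be blinded.

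**3. Who collects outcomes.** Blinding: research midwives who may have randomised also collect outcome data from the notes. Randomisation: these midwives are the likeliest randomisers.

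**4. Does the safeguard separate the two roles?** Take the two possible abstractors.
- A midwife who did not randomise the woman, was not in theatre, and reads only post-natal notes can stay blind, and the safeguard works.
- A midwife who randomised the woman knows the arm before she opens any notes, and the safeguard has no effect.

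No sentence in the article rules out the second case for notes abstraction. Statement 1, being unqualified, is therefore not delivered by the arrangements in statements 2 and 3.

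**5. Where treatment is recorded (secondary).** The Blinding section says "there will only be recording of whether the intervention was applied on the theatre operation note and anaesthetic/operation chart". The Randomisation section adds a sticker in the patient notes and the relevant case report forms. The first statement concerns treatment applied and the second concerns treatment allocated, so they are not word-for-word opposites. But the word 'only' is the stated reason for blinding, and for that purpose a record of the allocation reveals as much as a record of the treatment.

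**6. Scale.** The number of women for whom one midwife does both tasks is not given and cannot be derived. For orientation, with 125 women per arm, moving one case between the two endometritis categories changes that arm's proportion by 1/125 = 0.8 percentage points. The preliminary full-trial calculation uses a difference of 8.3% − 4.3% = 4.0 percentage points. This shows how coarse the feasibility data are; it does not estimate bias.

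**The case against.** The best defence is that the overlap is only permitted. The article says midwives may randomise, names many other kinds of randomising staff, and speaks of a staff group. It never says that the same midwife randomises and abstracts a given woman. A condensed article may also leave the rota to the full protocol. This stands as a limit on size. A reader might infer from the Randomisation section that most women are affected, but the documents do not establish that. It does not rescue the claim, because the article itself asserts blinding of all notes-based collection and gives a reason that fails whenever the overlap occurs.

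A reader might also infer that the randomising midwife could make the telephone calls unblinded. The documents do not support this. The Blinding section separately requires the interviewer to be blinded, and a midwife who knows the arm cannot meet that requirement.

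The sticker and forms are weaker evidence than they look. The sticker is listed in the context of the main hospital records, and the hand-held post-natal notes are expressly kept clear. The wording on forms is limited to the relevant ones, which fits a separate randomisation or theatre form. Nothing says that outcome forms show the arm. What remains is a need to reconcile the two sections.

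Nor does the article say who decides between CDC-defined and clinical endometritis, so the exposure of that outcome is conditional on the decision being made from the notes by an unblinded abstractor.

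Finally, the sponsor will verify data collection in 10% of records. This checks accuracy. It is not described as blinded, and it does not remove the influence of knowing the arm.

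**Conclusion.** The blinding claim does not hold as written for notes-based outcomes. It fails for every woman whose randomising midwife also abstracts her outcomes. That proportion is unknown, and the article gives reason to expect it is not zero. The conclusion rests on one assumption, that the person randomising is told the allocation.

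The consequence is possible ascertainment bias in clinical outcomes taken from the notes, including endometritis. A reader might want to attach a biased risk ratio to this, but the documents give no misclassification rate from which to calculate one. For the feasibility study itself the harm is limited. The study is not powered for efficacy, the analyses are mainly descriptive, feasibility outcomes pool the arms, and the stop-go criteria are recruitment, adherence, follow-up and drop-out. The greater stake is that a process labelled blinded goes into the full trial untested. The inconsistency over where treatment is recorded is secondary and needs reconciling.

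**What to change.** State in the Blinding section that, for each woman, anyone who randomised her or was in theatre with her does not abstract her outcomes. Use existing staff, and confirm that outcome forms do not carry the allocation. Where a site cannot arrange this, have the abstractor record whether she knew the allocation, and report the proportion among the feasibility outcomes so that the full trial can plan on it.

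If neither is adopted, restrict the blinding claim in the Feasibility study design and Blinding sections to the women (as an attempt) and the telephone interviewer.

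In either case, reconcile the Randomisation and Blinding sections on where allocation and treatment applied are recorded and which of those records an abstractor sees.

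The cost is a rota rule, one item on a form and some rewording, with slightly less flexible scheduling at small sites. The trial was already recruiting when the article was submitted, so for women whose outcomes have already been abstracted the change may be limited to restating the claim. The separation of roles should in any case be written into the full-trial protocol.

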### Intervention

Chlorohexidine gluconate 0.05% or chlorohexidine acetate 0.05% will be used to perform vaginal cleansing. The active ingredient is chlorhexidine 0.05%. This is indicated within the British National Formulary for swabbing in obstetrics.

Fifty millilitres of antiseptic (chlorohexidine gluconate 0.05% or chlorohexidine acetate 0.05%) will be emptied into a sterile pot. A single swab/sponge mounted on a sponge holder soaked in the antiseptic will be used to clean the vagina prior to CS at the time of urinary catheter insertion, for guidance, we suggest the vaginal cleansing should take 30 s. Following the CS procedure, the vagina will be cleaned of excess blood as is standard practice with a dry swab. The application of the intervention is quick and familiar to the doctors performing the surgery due to their experience in gynaecological surgery where it is routine practice. All theatres’ standard operating procedures regarding swabs and instrument counts should be adhered to, to ensure patient safety. At all sites, staff will be asked to record if they have performed vaginal cleansing, and if performed, which antiseptic was used, on the CS operation note within the hospital notes.

